## Abstract

**Background:**

Glucose variability increases cardiometabolic disease risk. While many factors can influence glucose levels, postprandial glucose response is the primary driver of glucose variability. Furthermore, affect may directly and indirectly impact glucose variability through its effect on eating behavior. Continuous glucose monitors (CGMs) facilitate the real-time evaluation of blood glucose, and ecological momentary assessment (EMA) can be used to assess affect in real time. Together, data collected from these sources provide the opportunity to further understand the role of affect in glucose levels.

**Objective:**

This paper presents the protocol for a study that aims to (1) evaluate the feasibility and acceptability of using CGMs along with EMA in nondiabetic populations and (2) examine the bidirectional relationship between affect and glucose in nondiabetic adults with overweight or obesity using a CGM and EMA.

**Methods:**

Eligibility criteria for the study include participants (1) aged 18 to 65 years old, (2) with a BMI of ≥25 kg/m^2^, (3) who are able to read and write in English, and (4) who own a smartphone. Individuals will be excluded if they (1) have type 1 or 2 diabetes or have any other condition that requires glucose monitoring, (2) are pregnant, (3) use any medications that have the potential to alter blood glucose levels or interfere with the glucose sensing process, or (4) have a diagnosed gastrointestinal condition or eating disorder. In a 14-day observational study, participants will wear a FreeStyle Libre Pro CGM sensor (Abbott) and will receive mobile phone–based EMA prompts 6 times per day (randomly within six 2-hour windows between 8 AM and 8 PM) to assess positive and negative affect. Participants will also wear a Fitbit Inspire 2 (Fitbit) to continuously monitor physical activity and sleep, which will be included as covariates in the analysis. Multilevel linear regression models will be used to evaluate the acute relationship between glucose level and affect.

**Results:**

Recruitment started in October 2022 and is expected to be completed in March 2023. We will aim to recruit 100 participants. As of December 12, 2022, a total of 39 participants have been enrolled.

**Conclusions:**

The results of this study will further elucidate the role of affect in glucose variability. By identifying affective states that may lead to glucose excursions, our findings could inform just-in-time behavioral interventions by indicating opportunities for intervention delivery.

**International Registered Report Identifier (IRRID):**

DERR1-10.2196/45104

## Introduction

Effective intervention strategies are required to reduce the immense burden of cardiometabolic disease. Standard behavioral interventions to reduce cardiometabolic disease risk are typically based on population averages [1,2]; however, variability in response to dietary interventions suggests the need for personalized approaches [3]. Precision approaches aim to tailor interventions to an individual’s unique characteristics and contexts [4,5]. For example, just-in-time adaptive interventions aim to facilitate behavior change by delivering an intervention at times and in contexts when individuals are more receptive to behavior change [6]. Identifying opportunities for change requires an understanding of the time-varying factors that influence behaviors.

The potential to measure time-varying factors has increased with the availability of wearable sensors. The use of continuous glucose monitors (CGMs) has resulted in the identification of glucose variability, that is, intraday fluctuations in blood glucose, as a risk factor for the development of cardiometabolic disease [7]. Greater glucose variability predicts increases in glycated hemoglobin (HbA_1c_) in both diabetic and nondiabetic populations [8,9]. Among persons with type 2 diabetes who maintain good glycemic control (HbA_1c_≤7.0%), greater glucose variability was an independent risk factor for coronary artery disease during a 10-year follow-up period [10]. Though evidence in nondiabetic populations is sparse, mechanistically, it has been proposed that glucose variability increases cardiovascular disease risk through increased oxidative stress and inflammation [11], an effect that has been observed among individuals with normal insulin function [12].

While several factors influence glucose levels (eg, stress, physical activity, etc), glucose variability is primarily driven by increases in postprandial glucose [13]. Controlled laboratory studies have demonstrated that several dietary factors impact postprandial glucose, such as meal composition [14,15], meal timing [16], and meal frequency [17]. In real-world settings, eating behavior, and thus glucose variability, is influenced by several individual-level factors. One example of an individual factor that influences eating behavior is affect [18-21]. The relationship between eating behavior and affect appears to be bidirectional as fatigue, stress, and negative mood are associated with increased cravings and food consumption [19-22], while variations in glucose in response to eating may relate to affective and physical feeling states [23-26]. However, research in this area has primarily relied on dietary assessment recall methodologies, which may be prone to bias and recall error [27]. Pairing data from CGMs with data on affect using ecological momentary assessment (EMA), which involves repeated sampling of affect in real time and in an individual’s natural environment, improves the validity of responses [28] and dramatically decreases the time between measurement of mood and glucose.

Combining CGM and EMA data to investigate the relationship between affective states and glucose variability presents an opportunity to support the development of precision interventions to prevent chronic disease by identifying situations that are likely to lead to large glucose increases (ie, an opportunity for change). A recent review [29] of mood and glucose variability in type 1 and 2 diabetes identified only 1 study that used CGMs and EMA to evaluate mood and glucose [25] and called for more research evaluating the relationships between mood or affect and glucose variability. To date, only a small (n=15) pilot study has combined EMA responses with CGM data to evaluate its association with affective and physical feeling states in nondiabetic samples [18]. Thus, the aims of this study are to (1) evaluate the feasibility of conducting a study using CGMs and EMA and (2) examine the bidirectional relationship between affect and glucose in adults using CGM and EMA data.

## Methods

This is a 14-day observational study. Enrolled participants (N=100) will wear a CGM and receive EMA prompts to assess affect 6 times per day over the 14-day period (detailed below).

### Ethics Approval

The study protocol was approved by the Texas A&M University Institutional Review Board (IRB2021-1412F).

### Participants

Participants will be recruited through online social media advertisements, flyers in community settings, and emails to community members who have indicated previous interest in research participation. Interested individuals will complete a brief web-based screening questionnaire to determine study eligibility. Inclusion and exclusion criteria for the study are outlined in Textbox 1.

Inclusion and exclusion criteria for study participation.
**Inclusion criteria:**
Aged 18 to 65 years oldHave a BMI of ≥25 kg/m^2^Able to read and write in EnglishOwn a smartphone
**Exclusion criteria:**
Diagnosed with type 1 or type 2 diabetes or any other condition that requires glucose monitoringPregnant womenUse of any medications that have the potential to alter blood glucose levels or interfere with the glucose sensing process (eg, corticosteroids, metformin, ascorbic acid, aspirin, acetaminophen, etc)Diagnosed with a gastrointestinal conditionDiagnosed with an eating disorder

### Baseline Visit

Upon confirmation of eligibility, participants will attend a baseline visit. Prior to completing any study-related activities, participants will sign an institutional review board–approved consent form. Participants will complete questionnaires to collect demographic data (age, sex, gender, race, ethnicity, and zip code), and study staff will measure participants’ height and weight. Height will be measured with a Seca 213 stadiometer (Seca GmbH). Two measurements will be taken and recorded in centimeters. If a discrepancy of greater than 0.5 cm is noted, additional measurements will be taken until 2 consecutive measurements within 0.5 cm occur. An average of those 2 measures will be recorded for height. Similarly, weight will be measured using a Seca Clara 803 scale, recorded in kilograms, and taken until 2 consecutive measures within 0.5 kg occurs.

#### Glucose Monitoring

Participants will wear a FreeStyle Libre Pro CGM sensor (Abbott) on the upper arm of the participant’s choosing for 14 days. The FreeStyle Libre Pro collects blinded interstitial glucose levels at 15-minute increments.

#### Affect

During the 14-day data collection period, participants will receive EMA prompts delivered to their smartphone via the Ethica mobile app (Ethica Data). Prompts will be delivered 6 times per day. One prompt will be delivered at a random time within each 2-hour window between 8 AM and 8 PM (8 AM-10 AM, 10 AM-12 PM, 12 PM-2 PM, 2 PM-4 PM, 4 PM-6 PM, and 6 PM-8 PM). Each prompt will consist of 10 Likert-scale items that will assess both positive and negative affect, with responses ranging from 1 (not at all) to 4 (extremely): “How (happy, cheerful, relaxed, stressed, anxious, angry, sad, energetic, tired, lonely) do you feel?” The survey will also include 2 “yes” or “no” questions: “Are you (bored, hungry) right now?”

The order of the 10 items will be randomized at each time point. Assessment questions have been validated for their use in daily or momentary assessment [30-32].

### Covariates

#### Physical Activity and Sleep

Each participant will be provided a Fitbit Inspire 2 (Fitbit) to track physical activity and sleep over the 14-day data collection period. In the primary analyses, these variables will be included as covariates, but collection of this data will also facilitate secondary analyses of the complex interaction effects of physical activity, sleep, and affect on glucose level. Data from the Fitbit devices will be processed using Fitabase (Small Steps LLC).

#### Survey

A baseline survey will collect participants’ demographic information and the following covariates:

Depression symptoms; Patient Health Questionnaire-9 (PHQ-9): the 9-item PHQ-9 is designed to measure depressive symptoms [33].Anxiety symptoms; Generalized Anxiety Disorder-7 (GAD-7): the 7-item GAD-7 is a brief scale to identify probable cases of generalized anxiety disorder and to assess symptom severity [34].UCLA (University of California, Los Angeles) Loneliness Scale: this is a 20-item scale designed to measure one’s subjective feelings of loneliness as well as feelings of social isolation with established validity and reliability [35].Self-Compassion Scale–Short Form (SCS-SF): the 12-item SCS-SF is a short version of the original Self-Compassion Scale [36].Coping Strategy Indicators (CSI): the 33-item CSI is a self-report measure of situational coping encompassing the strategies of avoidance, problem-solving, and seeking social support [37].Salzburg Stress Eating Scale (SSES): the 10-item SSES questionnaire measures eating in response to stress [38].Weight Efficacy Lifestyle Questionnaire–Short Form (WEL-SF): the 8-item WEL-SF measures patients’ confidence in their ability to control eating behavior in challenging situations and was developed as a brief measure for use in research and clinical practice [39].Food Cravings Questionnaire-Trait-reduced (FCQ-T-r): the 15-item FCQ-T-r questionnaire measures the frequency and intensity of food craving experiences [40].Experience in Close Relationship Scale (ECR-S): the 12-item ECR-S questionnaire concerns romantic relationships [41].

### Follow-up Visit

Upon completion of the 14-day study, each participant will be asked to complete a follow-up visit. Poststudy weight will be measured at the visit (to potentially control for weight change in statistical analysis), and participants will complete a questionnaire to assess their experience during the study. The questionnaire will include both Likert-scale and open-ended questions aimed at identifying any barriers to device compliance. Participants will return the Fitbit and CGM sensor at this follow-up visit.

### Analysis

We will determine compliance to CGM and Fitbit wear (% of wear time) and response rates to EMA prompts (% of prompts responded to). Predetermined compliance values (CGM and Fitbit wear ≥80%) and EMA response rates (75%) will be used to assess the feasibility of the study procedures.

Multilevel linear regression models, which adjust the standard errors for the clustering of EMA and glucose data within individuals and partition the variance of between- and within-person effects, will be used to evaluate the acute relationship between glucose level and affect. The following two outcome variables will be evaluated: (1) average glucose level in the time period between 2 EMA prompts and (2) occurrence of a glucose excursion (defined as a glucose level greater than 1 SD above the mean 24-hour glucose level). Predictor variables will be 2 separate composite scores for positive affect (average of “happy,” “cheerful,” “relaxed,” and “energetic”) and negative affect (average of “stressed,” “anxious,” “angry,” “sad,” and “tired”). Secondary analyses will be used to predict the interaction effects of physical activity, sleep, and affect on glucose level. Similar models will evaluate positive and negative affect as the outcome variable and average glucose level in the hour prior as the predictor. Covariates in the model will include age, sex, BMI, time of day, day of week, physical activity since the previous EMA prompt, and previous night’s sleep. Additional baseline measures will be evaluated as potential covariates and included in the final model if found to significantly improve model fit. Instances of missing EMA or CGM data will be excluded from the analysis.

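### The only model class named, multilevel linear regression, is also applied to the yes/no excursion outcome, whose variance and range it does not match

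*Protocol article*

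**What the plan says.** Under Analysis, the protocol article introduces its models as "Multilevel linear regression models, which adjust the standard errors for the clustering of EMA and glucose data within individuals". The next sentence sets out what they are for: "The following two outcome variables will be evaluated: (1) average glucose level in the time period between 2 EMA prompts", and, as the second outcome, "occurrence of a glucose excursion (defined as a glucose level greater than 1 SD above the mean 24-hour glucose level". The first is continuous. The second either happens or does not.

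The Methods paragraph of the abstract agrees: "Multilevel linear regression models will be used to evaluate the acute relationship between glucose level and affect". No other model class appears in the article. The later sentence on similar models concerns affect as the outcome and average glucose in the preceding hour as the predictor, so it does not supply a model for excursions.

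Two other statements bear on the point. The adjustment set is given as "Covariates in the model will include age, sex, BMI, time of day, day of week", followed by physical activity and sleep, so time of day is expected to matter. The Introduction says that "glucose variability is primarily driven by increases in postprandial glucose", which is a reason to expect excursions to cluster around meals.

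**The concern.** A multilevel linear model assumes a residual variance that is the same at every level of risk and a mean that can take any value. Neither is true of a 0/1 outcome. Its variance is fixed by its mean, and the mean is a probability. The standard-error adjustment that the plan describes deals with repeated measures within a person. It does not deal with a variance that changes with risk. The section also relies on the model to separate within-person from between-person variation, and one Gaussian residual variance misdescribes the within-person part of a binary outcome.

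The excursion outcome is one of only two glucose outcomes named. According to the Discussion, the study is meant to help find the situations in which excursions occur. For that purpose, fitted risks that cannot be risks, and a single additive effect averaged over situations, are an awkward product. The model is stated in the text, so this is not a detail that the article leaves to a fuller plan.

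**Working it through.** **No figure to reproduce.** The article gives no excursion rate, effect size or power calculation. The mismatch itself is read from the text. The numbers below only show how much it could matter, and every rate and effect size in them is an assumption.

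**Inputs from the document.** The design is "Enrolled participants (N=100) will wear a CGM and receive EMA prompts to assess affect 6 times per day over the 14-day period". Six prompts give five between-prompt intervals within a day, so 5 × 14 = 70 per person and 7,000 for 100 people. With the 75% response target applied independently to both prompts, 0.75² = 0.5625 are usable, which is about 3,938. For the sensor, "The FreeStyle Libre Pro collects blinded interstitial glucose levels at 15-minute increments", which is about 8 readings in a two-hour interval.

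**Plausible base rates.** If readings were normal, P(reading > mean + 1 SD) = 1 − Φ(1) = 15.9%. If an interval counts as an excursion when any of its 8 readings exceeds the threshold, simulated first-order autocorrelation of 0.95, 0.90 and 0.80 gives 30%, 36% and 45%.

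**Step 1: variance, p(1−p).**

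| Risk p | p(1−p) |
|---|---|
| 5% | 0.048 |
| 16% | 0.134 |
| 30% | 0.210 |
| 50% | 0.250 |

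Between 5% and 50% risk the variance differs by 0.25 / 0.0475 = 5.3-fold.

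**Step 2: fitted risks outside 0-1.** Data were simulated for 100 people × 14 days × 5 intervals with 56% retained, and a random-intercept linear model was fitted. The ranges below cover person SDs of 0.3 and 0.8 on the logit scale.

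| Assumed interval risks | Share of fitted risks outside 0-1 |
|---|---|
| Flat 16% | 0 to 0.1% |
| 8% to 35% | 1.1% to 7.5% |
| 3% to 60% | 10.7% to 15.0% |

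A separate set of fits, using fixed-effect predictions, gave about 0.5-2% for flat, 2-3% for moderate and 9% for steep risks. The order is the same and the sizes depend on the assumptions.

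**Step 3: the test of affect.** Write s² for the variance of within-person affect in an interval and v = p(1−p). Ignoring the random intercept, the ratio of true to model-based variance of the affect slope is

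R = Σ(s²v) / (Σs² × mean v).

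Take interval risks of 50, 3, 60, 3 and 50%. Then v = 0.25, 0.0291, 0.24, 0.0291, 0.25, with sum 0.7982 and mean 0.1596.

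- s² equal in all intervals: R = 0.7982 / (5 × 0.1596) = 1. The standard error is right on average, however uneven v is.
- Affect SD multiplied by 1.6 in the high-risk and 0.4 in the low-risk intervals (s² = 2.56 and 0.16): R = 1.904 / (8.00 × 0.1596) = 1.49. The true SE is √1.49 = 1.22 times the model SE, so type I error is 2[1 − Φ(1.96/1.22)] ≈ 11%.
- The reverse pattern: R = 0.267 / (5.60 × 0.1596) = 0.30. The true SE is 0.55 times the model SE, and type I error is below 0.1%.

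Simulation agrees (150 runs each, Monte Carlo SE about 1.8 points at 5%): 6% with flat risk, 6% with steep risk and constant affect variance, then 9% and 0% under the two uneven patterns. A further check on the same design gave 4-6% with constant affect variance, and about 8.5% and 2.5% when it varied. A third check, with 1,000 runs and 84 complete windows per person, gave 4.6% and 5.1% under moderate and steep risks. At an odds ratio of 1.3 in its steep case, the mean model SE was 0.0044 against an empirical SD of 0.0045.

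**Step 4: the scale of the effect.** With odds o = p/(1−p), an odds ratio of 1.5 moves the risk to 1.5o/(1 + 1.5o). The rise is 2.3 points at a 5% base rate, 6.2 at 16%, 9.1 at 30% and 10.0 at 50%. A linear model without an affect-by-time term reports one figure for all. In the third check that figure equalled the true average marginal effect: 4.20 against 4.20 points with steep risks, and 5.09 against 5.09 with moderate risks.

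**The case against.** The best defence is that a linear model for a 0/1 outcome is an accepted method. Its slope is an average risk difference, which is a legitimate quantity, and steps 3 and 4 show that it is recovered without bias and, in the plainest settings, with sound standard errors. That stands. A reader might infer from the mismatch that the test of affect on excursions is invalid or that its effect estimate is biased. The documents do not support this: they say nothing to suggest that affect variance changes over the day, and without that the type I error stays near nominal. The uneven patterns in step 3 are also severe, with a 4-fold difference in affect SD.

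A reader might also infer that one additive slope must be wrong because the risk difference changes with the base rate. That follows only if the odds ratio is constant, which step 4 assumes. If the risk difference were constant, a single odds ratio would be the poor summary. Under either link, an affect-by-time term would give effects specific to an interval.

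Nor does the article state that excursion risk varies strongly over the day. The Introduction makes it plausible, but no rate is given, and with flat risk the out-of-range problem is small or absent. No individual risk prediction is planned, and just-in-time intervention appears only as later work.

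Finally, the wording may be shorthand. That is possible, but a linear model is named twice and no alternative once. If a linear probability model was intended, the text gives no sign of it: no risk-difference target and no variance estimator for binary data. This part of the objection does not remove the point.

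**Conclusion.** The point holds as a mismatch between the stated model and one stated outcome. Constant Gaussian variance is wrong for excursion occurrence whenever risk varies. Fitted risks can be impossible: between none and about 2% of them with risk flat near 16%, and roughly 1% to 15% with risk varying by time of day. Both ranges depend on assumed rates.

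The consequence for inference is conditional. Standard errors for the affect effect are close to right if affect variance is constant over the day. They become too small (type I error about 9%) or too large (about 0-3%) only if affect variance also changes with time of day, in step with risk or against it.

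Mean glucose and the affect scores as outcomes are unaffected, and so is the feasibility aim. This is something that should be fixed; it does not undermine the study.

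**What to change.** In the Analysis section, state that occurrence of a glucose excursion will be analysed by multilevel logistic regression with a random person intercept and separate within-person and between-person affect terms, and that results will be reported as odds ratios with marginal risk differences. Keep the linear model for mean glucose and for the affect scores. Amend the model sentence in the abstract's Methods paragraph to match. Do this before analysis, so that the scale is not chosen after the results are seen.

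The cost is two sentences, slightly more analysis work, and an effect measure on the odds-ratio scale, which the marginal risk differences help to make readable. Data collection and sample size do not change.

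### The model sentence names individuals as the only clustering unit; read in the ordinary way, its standard errors will be too small if affect and glucose both persist within days or if slopes differ between people

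*Protocol article*

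**What the plan says.** All places are in the protocol article, under Methods.

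- **Design.** The design opening states "Enrolled participants (N=100) will wear a CGM and receive EMA prompts to assess affect 6 times per day over the 14-day period". The Affect section adds "One prompt will be delivered at a random time within each 2-hour window between 8 AM and 8 PM". Each participant therefore has up to 14 × 6 = 84 prompts, grouped into days.
- **Model.** The Analysis section plans multilevel linear models "which adjust the standard errors for the clustering of EMA and glucose data within individuals" and "partition the variance of between- and within-person effects". One clustering unit is named and two sources of variance are separated. A day level, a serial residual structure, random slopes and the type of standard error are neither stated nor excluded.
- **Covariates.** Besides age, sex, BMI, time of day and day of week, the models include "physical activity since the previous EMA prompt, and previous night’s sleep". Sleep takes one value per day and is carried by up to six prompts. Secondary models examine interactions of activity, sleep and affect.
- **Both directions.** Similar models take affect as the outcome and mean glucose over the preceding hour as the predictor.

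The article states no significance level and gives no serial or day-level correlation for either series.

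**The concern.** The target is an acute, within-person effect. A person-level random intercept removes stable differences between people, but it treats all of one person's prompts as equally related, whether 2 hours or 10 days apart. Any tendency of affect and glucose to carry over between adjacent windows, or to share good and bad days, stays in the residuals. Differences between people in the affect-glucose slope stay there too.

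If those residuals are treated as independent, the sum over prompts of predictor times residual varies more than the model assumes, and confidence intervals are too narrow. Both directions of the hypothesised relationship are exposed, so chance could too readily be read as support for it. Sleep is more exposed than affect because it is constant within a day. This is a matter of error structure only: it arises even with no confounding and a true effect of zero.

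**Working it through.** The article gives no power, alpha or correlation figure, so there is nothing of its own to reproduce. The check asks how often a test rejects under no effect.

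**Inputs from the article:** 100 participants, 14 days, 6 prompts a day, which is 100 × 14 × 6 = 8,400 prompts. The feasibility thresholds are 75% EMA response and 80% CGM wear. Used as rates, they leave r = 0.75 × 0.80 = 0.60 of moments usable.

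**Assumptions:** two-sided 5% level; moments lost at random; continuous outcome; within-day lag-1 correlation φ of 0 to 0.5 per 2-hour step; day-level share d of within-person variance of 0 to 0.3; slope SD of 0 or 0.1 of an outcome SD.

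**Closed form.** The within-day correlation at lag k is ρ(k) = d + (1 − d)φ^k. For a person-centred predictor x and outcome y, the true variance of the slope divided by the variance the random-intercept model reports is approximately

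D = 1 + r × (2/6) × S, with S = Σ (6 − k) ρx(k) ρy(k), k = 1 to 5.

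The rejection rate is 2Φ(−1.96/√D).

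*Affect, both series correlated, r = 0.60*
- φ = 0.3, d = 0: S = 5(0.09) + 4(0.0081) + 3(0.0007) + … = 0.485; D = 1 + 0.2 × 0.485 = 1.097; rejection 6.1%.
- φ = 0.3, d = 0.2: ρ = 0.44, 0.272, 0.222, 0.206, 0.202; S = 1.537; D = 1.307; rejection 8.7%.
- φ = 0.5, d = 0.2: ρ = 0.6, 0.4, 0.3, 0.25, 0.225; S = 1.8 + 0.64 + 0.27 + 0.125 + 0.051 = 2.886; D = 1.577; rejection 11.9%.

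*Only one series correlated:* every product ρx(k)ρy(k) is zero, so D = 1 and rejection is 5.0%.

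*Slopes differing between people, no serial correlation:* with n = 84 × 0.60 = 50.4 moments per person and slope variance 0.1² = 0.01, D ≈ 1 + 50.4 × 0.01 = 1.504; rejection 11.0%.

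*Sleep:* ρx(k) = 1, so only the outcome's correlation matters.
- d = 0.2, φ = 0: S = 0.2 × 15 = 3.0; D = 1.6; rejection 12.1%.
- d = 0, φ = 0.5: S = 2.5 + 1 + 0.375 + 0.125 + 0.031 = 4.031; D = 1.806; rejection 14.5%.
- d = 0.2, φ = 0.3: S = 4.568; D = 1.914; rejection 15.6%.

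*Sleep by affect:* multiplying affect by a day-constant variable leaves its within-day correlation unchanged. D is therefore the same as for affect: 8.7% for φ = 0.3, d = 0.2 and 11.9% for φ = 0.5, d = 0.2.

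**Simulation, true mean effect zero.** Model-based errors from a person-intercept model are compared with participant-clustered robust errors.

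| Scenario | Usable | Model-based | Robust |
|---|---|---|---|
| Affect, φ 0.3 in both | 60% | 6.0% | 4.6–5.5% |
| Affect, φ 0.3, d 0.2 in both | 60% | 8.8% | 4.6–5.5% |
| Affect, φ 0.5, d 0.2 in both | 60% | 11.5% | 4.6–5.5% |
| Affect, slope SD 0.1 only | 60% | 11.4% | 4.6–5.5% |
| Sleep, outcome d 0.2 | 60% | 12.4% | 4.6–5.5% |
| Sleep, outcome φ 0.5 | 60% | 15.2% | 4.6–5.5% |
| Affect, no correlation | 75% | 5.0% | 5.3% |
| Affect, only glucose correlated (φ 0.5, d 0.3) | 75% | 4.5% | 4.8% |
| Affect, only affect correlated (φ 0.5, d 0.3) | 75% | 5.2% | 5.3% |
| Affect, φ 0.5, d 0.3 in both | 75% | 15.3% | 4.3% |

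The 60% rows used 6,000 replicates (standard error at 5%: √(0.05 × 0.95/6,000) = 0.3 points), and their robust column is the range over all scenarios of that run. The 75% rows used 2,000 replicates (0.5 points). In the last row the model standard error was 0.74 of the true one; the closed form gives D = 1 + 0.25 × 3.805 = 1.951 and 1/√D = 0.72. The sleep-by-affect interaction simulated at 60% gave 7.8% to 10.5%. Over all runs the robust errors rejected between 4.3% and 5.8% of the time.

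**The case against.** **The text does not commit to the model that fails.** No random-intercept-only structure, independent residuals or model-based errors are stated. Days lie inside individuals, so errors that allow arbitrary dependence within individuals already cover them, and the sentence can be read that way. This stands. A reader might infer that the planned standard errors are too small as a matter of fact; the article does not support that. What remains is that the adjustment is credited to the multilevel model and robust errors are not mentioned, so the ordinary reading is a two-level model with model-based errors.

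**A condensed article may leave covariance detail to a fuller plan.** True, and silence about a residual structure would not be a finding. Here, however, the sentence claims a property, adjusted standard errors, and under its ordinary reading that property can fail.

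**The inflation is conditional.** This also stands. Correlation in one series alone does not inflate the affect test, and mild values do little: φ = 0.3 alone gives about 6%, and so does a slope SD of 0.05. With a day-level share of 0.05 alone, affect stays at about 5% and sleep reaches 7% to 8%.

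**Planned covariates may absorb the dependence.** Time of day and day of week are patterns shared by everyone and cannot remove one person's bad day. With these, activity and sleep in the model (1,500 runs, 60% usable, covariates given no effect on the outcome), rejection was 8.3% for φ = 0.3, d = 0.2 and 11.5% for φ = 0.5, d = 0.2, against 5.0% and 4.9% with robust errors. If the covariates do explain part of the outcome, the inflation could be smaller.

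**Sleep is a covariate, and the planned secondary tests are interactions.** Fair. The sleep main effect is not the main target, but the sleep-by-affect term is inflated too, by about the same amount as affect.

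**Conclusion.** The point holds conditionally. Under a person-level random intercept with independent residuals and model-based errors, the within-person affect-glucose test is anti-conservative if both series persist within days or if slopes differ between people. The sleep term is anti-conservative if the outcome alone is correlated within days.

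At an assumed two-sided 5% level and 60% of moments usable, the rates under no effect are:
- affect: about 6% (lag-1 correlation 0.3 only) to 12% (lag-1 0.5 plus 20% day-level variance);
- affect with slope SD 0.1 and no serial correlation: about 11%;
- sleep: about 12% to 16%;
- sleep by affect: about 8% to 11% in the scenarios run, and less with weaker correlation.

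The correlations, the slope SD and the 5% level are assumptions; only the design counts and the two thresholds behind the 60% come from the article. The simulated outcomes were continuous, so the figures do not describe the binary excursion outcome. A reader might also conclude that a three-level autoregressive model is required. The results do not support that, since robust errors alone kept the test near its nominal level.

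**What to change.** In the Analysis section, extend the model sentence to say: *Inference on all fixed effects, in the affect-to-glucose and glucose-to-affect models and in the sleep and activity interaction models, will use participant-clustered robust standard errors (100 clusters).*

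A participant-level random slope, a day-level random intercept or a serial residual structure may be added but is optional. If such a term does not converge, it can be dropped while the robust errors are kept.

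The cost is one clause and no new data. The downside is somewhat wider confidence intervals.
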